#### **5.5.6 End of Intervention; Start of Follow-up**

An episode of diarrhoea will be defined as two or more liquid stools (Bristol Stool Scale types 5, 6 and 7) that is greater than normal for the inpatient over a 24 hour period.

The frequency and duration of diarrhoea / constipation will be monitored.

Patients' quality of life (WHO-QoL: *Spinal Cord* 48:762-769; *Spinal Cord* 50:112-118), medication charts (especially antibiotics, laxatives, anti-diarrhoeal agents, proton pump inhibitors and H2 blocker) and nutrition risk scores (Wong *et al.*, 2012) will be assessed **at baseline (within 24 hours of starting intervention, Yakult/placebo), 7 +/- 3 days after finishing course of antibiotics and at follow up (30 +/- 3 days after finishing course of antibiotics).**

Duration of hospital stay will be recorded on the patient's hospital record.

Bowel function will also be monitored throughout (i.e. stool type; duration of diarrhoea / constipation relapse).

In addition, faecal samples will be routinely acquired at in the event of diarrhoea, and at the end of intervention. These samples will be frozen and stored, before sending to YHER for microbiological analysis, including TaqMan PCR analysis of toxigenic *C. difficile*. Technique will be based on the paper by Kubota *et al.* (2014).

#### **5.5.7 Study endpoint / closing assessment**

An episode of diarrhoea will be defined as two or more liquid stools (Bristol Stool Scale types 5, 6 and 7) that is greater than normal for the inpatient over a 24 hour period. The frequency and duration of diarrhoea / constipation will be monitored.

Patients' quality of life (WHO-QoL: *Spinal Cord* 48:762-769; *Spinal Cord* 50:112-118), medication charts (especially antibiotics, laxatives, anti-diarrhoeal agents, proton pump inhibitors and H2 blocker) and nutrition risk scores (Wong *et al.*, 2012) will be assessed **at baseline (within 24 hours of starting intervention, Yakult/placebo), 7 +/- 3 days after**

**finishing course of antibiotics and at follow up (30 +/- 3 days after finishing course of antibiotics).** Duration of hospital stay will be recorded on the patients' hospital record.

Bowel function will also be monitored throughout (i.e. stool type; duration of diarrhoea / constipation relapse).

In addition, faecal samples will be routinely acquired at the end of intervention (7 +/- 3 days after antibiotics course). These samples will be frozen and stored, before sending to YHER for microbiological analysis, including TaqMan PCR analysis of toxigenic *C. difficile*. Technique will be based on the paper by Kubota *et al.* (2014).

In order to comply with Ethical requirements, Yakult UK would deliver two weeks of Yakult Light to all subjects when they finish the trial. All patients taking Yakult and not in the trial, should be given Yakult Light (blue top) to avoid any muddle with those in the trial who will be drinking red top bottles.

#### **5.5.8 Logistics Stool Specimen**

In case participants develop diarrhoea, stool samples will be collected and sent to the trust microbiology laboratory for *Clostridium difficile* toxins analysis.

**Collection:** Ward nurses will be responsible for collecting stool specimens at baseline and at follow-up for non-routine analysis (SARSTEDT tubes). (Appendix 2)

**Transport:** Collected stool specimen will be delivered to Buckinghamshire Healthcare NHS Trust's laboratory by hospital porter [equivalent in other SCI centre's site]

**Preparation for testing:** Baseline and follow up specimen will be collected in SARSTEDT tubes. Diarrhoeal stool specimen x1 will be transfer into 3 specimen pot for further analysis (1x *Clostridium difficile* toxin analysis (in NHS laboratory), 1x PCR/rt-PCR analysis (at YHER), 1x reserve)

#### **Analysis:**

- *Clostridium difficile* toxin test will be carried out in BHT's microbiology laboratory under supervision of [name] [name] (Consultant Microbiologist)
- Diarrhoeal samples that fall within the trial definition will be tested by the NHS laboratory, and extra samples will be collected: x 1 will be collected for PCR / rt-PCR analysis by YHER, and 1 x reserve (stored).
- If patients develops diarrhoea within 72 hours admission to the SCI centre, then the microbiology department will look for other pathogens that may have been acquired in the community (e.g. *Salmonella*, *Shigella*, *Campylobacter*)
- The remainder of the stool specimen will be stored in a dedicated fridge (4 °C) for up to 12 hours before being stored at -20 °C;
- A spoonful of the stool sample (approximately 200 mg) will be placed in a tube (SARSTEDT, Cat. No. 80.734.001) with 2 ml of RNAlater

(<http://www.sarstedt.com/pdf/prospekte/en/537.pdf>). These samples can be frozen at -20 °C for 6 months, for delivery to Yakult Europe laboratory for TaqMan PCR analysis of toxigenic *C. difficile* according to the manufacturer's instructions with technique described previously (Kubota *et al.* 2014).

### **Transport of stool specimen to YHER**

Citysprint couriers will be used to courier samples to YHER. Contact details: [name] (Clinical Trials Co-Ordinator, [contact]). Samples will not have any patient identifiable information (with a study project number).

The PI will have a date code and/or additional code to indicate the different samples as follows:

**Routine sample #1 (baseline)** = collected at baseline within 24 hours of starting intervention (Yakult/placebo). The patient will only just have started antibiotics and intervention (i.e. Yakult or placebo). **Data code: 2 X X X**

**Routine sample #2 (ABx+7d)** = collected seven days after the patient stops antibiotics (with a window of  $\pm 3$  days), and thus on the day they stop intervention (Yakult/placebo). **Data code: 3 X X X**

**Routine sample #3 (ABx+30d)** = collected 30 days after the patients stops antibiotics (with a window of  $\pm 3$  days), and thus 23 $\pm 3$  days after they stop intervention (Yakult/placebo). **Data code: 4 X X X**

### **Analysis plan**

First YHER will test all **samples#3 (ABx+30d)**. If toxigenic *C. difficile* is found at a prevalence of  $\geq 2\%$ , then YHER will test **samples#1 (baseline)**.

If a subject develops diarrhoea, the above routine micro testing will be done at Stoke Mandeville. Part of the diarrhoea sample will also be stored in a tube a frozen, before sending for further analysis by YHER. YHER will analyse all diarrhoea samples using TaqMan PCR analysis. (Diarrhoea sample will be code as **5 X X X**)

The decision on whether to test **samples#2 (ABx+7d)** will be taken later.

Samples will be kept at YHER for further microbiota analysis at a later date. This is written into the protocol, and will be highlighted in the informed consent form where patients will be reassured that the samples (and results) will be anonymous.

Analysed data will be sent back to Principal Investigator for decoding (patient's identity).

## **6. Definitions of outcomes and study variables**

### **6.1 Primary outcome: Occurrence of antibiotic-associated diarrhoea (AAD)**

In the current study, occurrence of antibiotic-associated diarrhoea is defined as two or more loose stools (Bristol Stool Scale type 5 or above) up to 30 days after finishing antibiotics.

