| Secondary objective                       | Analyse the effect of LcS on (i) occurrence of C. difficile diarrhoea; (ii) duration of diarrhoea; (iii) gastrointestinal microbiota and (iv) quality of life                                                                                                                                                                                                                                                                                                                                                                                                                                                                                                                                                    |
| Hypothesis                                | It is hypothesised that maintenance of a healthy commensal microbiota during antibiotic treatment by administration of a daily probiotic ( Lactobacillus casei Shirota, as Yakult) will significantly reduce the occurrence of AAD and CDAD, and thus improve quality of life in spinal cord injury patients over time in comparison to the placebo control                                                                                                                                                                                                                                                                                                                                                      |
| Primary endpoint                          | Occurrence of antibiotic-associated diarrhoea (i.e. 2 or more loose stools, Bristol Stool Scale type 5 or above) up to 30 days after finishing probiotic/placebo                                                                                                                                                                                                                                                                                                                                                                                                                                                                                                                                                        |

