#### 5.5.2 Study procedure: opening assessments

After having obtained informed consent (1x copy to patients; 1x copy in medical notes; 1 x original in the investigator site file), basic patient's clinical characteristics and baseline measurements, as outlined on the Case Report Form (CRF, see [Item 12.1](#)), will be collected. No intervention will be administered prior to the completion of the study opening visit.

- Baseline demographics and clinical data
- Record use of medications (including use of antibiotics, laxatives, anti-diarrhoeal agents, proton pump inhibitors, H2 blocker)
- Nutrition risk scores – Spinal Nutrition Screening Tool (Wong et al, 2010, 2012)

- Quality of Life evaluation – WHO-QoL BREF ([http://www.who.int/substance\\_abuse/research\\_tools/en/english\\_whoqol.pdf](http://www.who.int/substance_abuse/research_tools/en/english_whoqol.pdf))
- Bowels function measures – stool type, duration of diarrhoea  
Definition of diarrhoea: two or more loose stools, Bristol Stool Scale (O'Donnell LD, 1990) type 5 or above.  
Constipation: using Rome III criteria: Functional constipation ([http://www.romecriteria.org/assets/pdf/19\\_RomeIII\\_apA\\_885-898.pdf](http://www.romecriteria.org/assets/pdf/19_RomeIII_apA_885-898.pdf)) (Drossman DA, 2006).
- Stool Specimen analysis (Kubota *et al.* 2014)  
One sample will be taken, frozen and stored frozen and then sent to YHER for TaqMan PCR analysis of toxigenic *C. difficile*. This analysis will be dependent on available resources at YHER. Further microbial analysis may also be done. This will be in the participant information sheet and on the consent form.

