**If a patient misses intervention for more than 3 days, they will be withdrawn from the study.**

We will analyse the data using intention-to-treat principle.

An episode of diarrhoea is defined as two or more liquid stools (Bristol Stool Scale types 5, 6 and 7) that is greater than normal for the inpatient over a 24 hour period.

The frequency and duration of diarrhoea / constipation will be monitored.

Patients' quality of life will be assessed by WHO-QoL BREF questionnaire. Furthermore, medication charts (especially antibiotics, laxatives, anti-diarrhoeal agents, proton pump inhibitors and H2 blocker) and nutrition risk scores (Wong *et al.* 2010, 2012) will be assessed at baseline, 7 days after finishing course of antibiotics and 30 days after finishing course of antibiotics (follow up).

Duration of hospital stay will be recorded on the patients' hospital record.

Bowel function will also be monitored throughout (i.e. stool type; duration of diarrhoea / constipation relapse) by health care staff.

In addition, faecal samples will be routinely acquired at **baseline (within 24 hours of starting intervention, Yakult/placebo), 7 +/- 3 days after finishing course of antibiotics, at follow up (30 +/- 3 days after finishing course of antibiotics), and in the event of diarrhoea.** Study samples will only be collected and processed Mon-Fri, therefore a window period of +/- 3 days for the day 7 and day 30 post-antibiotics course. These samples will be frozen and stored, before sending to YHER for microbiological analysis, including TaqMan PCR analysis of toxigenic *C. difficile*. Technique will be based on the paper by Kubota *et al.* (2014).

Faecal samples from any patient developing diarrhoea will be tested by the hospital according to normal practice and a further sample stored for further analysis by the external laboratory (YHER).

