#### **6.2.2 Duration of diarrhoea**

In the current study the duration of diarrhoea, defined as two or more loose stools, Bristol Stool Scale type 5 or above, will be collected in addition to the sole occurrence of diarrhoea.

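### The protocol defines its primary event in two incompatible ways, with and without a 24-hour period and a comparison with usual habit, and does not say which one decides the endpoint

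*Protocol*

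**What the plan says.** Four places in the protocol use a definition based only on the number and type of stools:

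- Section 6.1, the formal primary outcome: "occurrence of antibiotic-associated diarrhoea is defined as two or more loose stools (Bristol Stool Scale type 5 or above". The only time limit there is the end of the observation window, 30 days from the last day of antibiotics.
- The synopsis, primary endpoint: "2 or more loose stools, Bristol Stool Scale type 5 or above) up to 30 days after finishing probiotic/placebo".
- Section 5.5.2, opening assessments: "Definition of diarrhoea: two or more loose stools, Bristol Stool Scale". The types counted are again 5 and higher.
- Section 6.2.2, duration of diarrhoea: "defined as two or more loose stools, Bristol Stool Scale type 5 or above".

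Sections 5.5.5, 5.5.6 and 5.5.7, which cover the intervention, follow-up and closing phases, use another. There an episode is two or more stools of types 5, 6 and 7 "that is greater than normal for the inpatient over a 24 hour period".

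Section 6.1 does not refer to the episode definition, and no section ranks one above the other. Section 5.5.8 speaks of a single trial definition for diarrhoeal samples without saying which it means. Appendix 2 has stool type and occurrence of diarrhoea recorded daily.

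**The concern.** The primary outcome is a yes/no classification of each patient, and two written rules can classify the same patient differently. Under 6.1 as written, the only time limit is the whole observation window. Two isolated type 5 stools days or weeks apart would make a patient a case of antibiotic-associated diarrhoea (AAD). Under 5.5.5 they would not.

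Two things are at stake. First, a trial with two written versions of its only primary outcome leaves room to pick one once results are known, whatever the difference in counts. Second, if the looser version were applied, loose stools unrelated to antibiotics could enter both arms and dilute the difference. The same ambiguity reaches the exclusion for diarrhoea in the 7 days before intervention, the duration outcome, and the hospital testing of diarrhoeal samples that feeds the *C. difficile* outcome.

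**Working it through.** **1. The definitions side by side**

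| Element | Synopsis, 5.5.2, 6.1, 6.2.2 | 5.5.5, 5.5.6, 5.5.7 |
|---|---|---|
| Number of stools | two or more | two or more |
| Bristol type | 5 or above | 5, 6 and 7 |
| Period containing the stools | none given | 24 hours |
| Compared with usual habit | no | yes |

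The Bristol types are the same, so over a common window every case in the right-hand column is also a case in the left-hand column. The reverse need not hold. The left-hand count is therefore equal or higher in each arm. This direction is certain, but the size is not.

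**2. The plan's own figure**

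Inputs from section 7.2: p1 = 0.563, p2 = 0.384, difference d = 0.179, α = 0.05 (taken as two-sided), power 90%. With pooled variance and no continuity correction,

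n = [1.960·√(2·p̄·(1−p̄)) + 1.282·√(p1(1−p1) + p2(1−p2))]² / d², where p̄ = 0.4735.

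This gives n = 162 per group, and 162/0.90 = 180 per arm, both as stated. Power at 162 per group is 90.1%. The sample-size arithmetic is not at fault.

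**3. Illustration of dilution**

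Two assumptions are needed, and the documents support neither: (a) the planning rates were measured under the stricter definition; (b) a share b of non-cases under that definition is counted as AAD, equally in both arms. Then p′ = p + (1 − p)·b, and the difference becomes d·(1 − b). For b = 0.20: 0.563 + 0.437·0.20 = 0.650 and 0.384 + 0.616·0.20 = 0.507, with difference 0.179·0.80 = 0.143.

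| b (assumed) | Rates | Difference (points) | Power at 162 per group | n per group for 90% |
|---|---|---|---|---|
| 0 | 56.3% v 38.4% | 17.9 | 90% | 162 |
| 5% | 58.5% v 41.5% | 17.0 | 87% | 180 |
| 10% | 60.7% v 44.6% | 16.1 | 83% | 200 |
| 20% | 65.0% v 50.7% | 14.3 | 74% | 248 |
| 30% | 69.4% v 56.9% | 12.5 | 65% | 310 |

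**4. Why b cannot be pinned down**

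The protocol gives no rate of sporadic loose stools. Assume that they occur independently (Poisson) over 37 days, that is, an assumed 7-day antibiotic course plus the 30 days in 6.1. With m the expected number of stools, the chance of at least two is 1 − e^(−m)(1 + m).

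| Assumed rate | At least two in the window | At least two on one calendar day |
|---|---|---|
| One per 30 days | 35% | 2% |
| One per 14 days | 74% | 9% |
| One per 7 days | 97% | 29% |

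The 24-hour condition can matter a great deal, but the answer depends almost wholly on an unknown rate. These percentages are not estimates of b and do not feed the table in step 3.

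**The case against.** The best defence is that 6.1 is shorthand. The fuller definition appears in all three monitoring phases, section 5.5.8 refers to one trial definition, and Appendix 2 makes the day the unit of recording. Staff may well have applied the 24-hour rule throughout, and a statistical analysis plan, not shown here, may settle the matter. This stands as a limit on the consequences. It does not remove the contradiction, because the protocol states both rules and the looser one sits in the section that defines the primary outcome.

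A reader might infer more than the documents support:

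- **That AAD is in fact inflated and power lost.** Inflation follows only if 6.1 is applied literally. Loss against plan also needs the planning rates to have used the stricter definition. Section 7.2 says only that they are pilot data on patients with diarrhoea. If the pilot used the looser wording, its rates already contain such events.
- **That patients with habitually loose stools would routinely count as cases.** The exclusion for diarrhoea in the preceding 7 days largely answers this: under the 5.5.2 wording, two type 5 or above stools in that week already exclude the patient. A gap remains if the exclusion is screened with the episode wording, which discounts what is normal for the patient.
- **That the change from loose to liquid matters.** Both words are tied to Bristol types 5 to 7, so no classification changes.

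**Conclusion.** The point holds as an internal contradiction in the primary outcome, and it should be corrected. That rests on the text alone and needs no assumption. The direction is also firm: applied literally, 6.1 gives an AAD rate in each arm equal to or higher than the episode definition would give.

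The size is not established. A fall in power from 90% to about 83% or 74% is hypothetical. It depends on an assumed 10% or 20% of non-cases being counted equally in both arms, and on planning rates measured under the stricter definition. The case for correction rests on the primary outcome not being uniquely defined, not on those figures.

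**What to change.** Before unblinding, amend the protocol to one primary definition and state it identically in the synopsis and sections 5.5.2, 6.1 and 6.2.2. The episode wording in 5.5.5 to 5.5.7 is the natural candidate, since it is already in the protocol and the daily stool record allows the 24-hour condition to be derived by program. State how 'normal' is determined for each patient from the opening bowel assessment. As a sensitivity analysis, report the 24-hour count without the 'normal' condition.

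The synopsis and 6.1 also run the 30-day window from different events (end of study product v end of antibiotics). That is a separate matter, but the same amendment should reconcile it.

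The cost is more than an edit of wording. Section 12 requires a change to the protocol to go to the Research Ethics Committee as an amendment. This is version 3.2 of May 2018 with completion estimated for Q3 2018, so time is short. Somewhat fewer events would be counted than under the literal 6.1. The baseline for 'normal' may be incomplete: 5.5.2 lists stool type and duration of diarrhoea at opening but not usual stool frequency, and patients may already have started antibiotics by then. The sensitivity analysis is there to cover that weakness.

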## 17 Appendices

### Appendix 1: Study flow chart

[figure not shown]

| Appendix 2. Study data collection - summary | Screening / Opening visit | (Probiotic / Placebo allocation) | Monitor Daily (+) weekly (x) throughout the study | 7 days after finishing antibiotics course | 30 days after finishing antibiotics course |
|-----------------------------------------------------------|----------------------------------|-----------------------------------------|----------------------------------------------------------|--------------------------------------------------|---------------------------------------------------|
| Eligibility                                        | X                                |                                         |                                                          |                                                  |                                                   |
| Informed consent                                   | X                                |                                         |                                                          |                                                  |                                                   |
| Demographics & Clinical data                   | X                                |                                         |                                                          | X                                                | X                                                 |
| Compliance                                         |                                  |                                         | +                                                        | X                                                |                                                   |
| Record use of medications                          | X                                |                                         |                                                          |                                                  |                                                   |
| Proton pump inhibitor                                     |                                  |                                         |                                                          | X                                                | X                                                 |

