| H 2 blocker                                    | X                                |                                         |                                                          | X                                                | X                                                 |
| Anti-diarrhoeal agent                                     | X                                |                                         |                                                          | X                                                | X                                                 |
| Antibiotics                                               | X                                |                                         | +                                                        | X                                                | X                                                 |
| Nutrition risk screening- SNST                     | X                                |                                         |                                                          | X                                                | X                                                 |
| Quality of life – WHO-QoL                          | X                                |                                         |                                                          | X +/- 3 days                                     | X +/- 3 days                                      |
| Bowel function assessment                          |                                  |                                         |                                                          |                                                  |                                                   |
| Stool type (Bristol scale)                                | X                                |                                         | +                                                        | X                                                | X                                                 |
| Occurrence of diarrhoea                                   |                                  |                                         | +                                                        | X                                                | X                                                 |

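### The AAD definition and the Appendix 2 schedule do not match the body text on the patient's normal stool pattern and on laxatives, so laxative-related cases could be counted without being identifiable

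*Protocol*

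**What the plan says.** **Primary outcome.** Section 6.1 defines AAD as "two or more loose stools (Bristol Stool Scale type 5 or above) up to 30 days after finishing antibiotics". The synopsis uses the same stool criterion. Neither mentions medication, a 24-hour window or the patient's usual pattern.

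**Episode definition in the procedures.** Sections 5.5.5, 5.5.6 and 5.5.7 define an episode as two or more stools of Bristol types 5 to 7, with the added condition "that is greater than normal for the inpatient over a 24 hour period".

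**Medication in the body text.** At the opening assessment (section 5.5.2), drug use is recorded, "including use of antibiotics, laxatives, anti-diarrhoeal agents, proton pump inhibitors" and H2 blockers. Section 5.5.5 then has "medication charts (especially antibiotics, laxatives, anti-diarrhoeal agents, proton pump inhibitors" and H2 blockers reviewed; these "will be assessed at baseline, 7 days after finishing course of antibiotics and 30 days after finishing course of antibiotics (follow up"). Sections 5.5.6 and 5.5.7 repeat this with a window of 3 days either side.

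**Medication in Appendix 2.** The schedule has a general row, "Record use of medications", ticked at opening only. Below it are named rows for proton pump inhibitors, H2 blockers, "Anti-diarrhoeal agent" and antibiotics. Laxatives have no row. Anti-diarrhoeals are ticked at opening, day 7 and day 30. Antibiotics, stool type, diarrhoea and constipation also carry the daily mark.

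**Use in the outcomes and analysis.** Section 6.2.2 defines duration by the same stool criterion. Section 7.4 plans a logistic regression for factors influencing diarrhoea and four subgroup factors. It names neither laxatives nor anti-diarrhoeals.

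**The concern.** The trial monitors constipation every day, so laxatives may well be started or increased during follow-up. A patient who then passes two type 5 stools meets section 6.1. The authors evidently saw that bowel drugs matter, because four sections tell staff to track them. Yet the table that summarises data collection leaves laxatives out of follow-up, and section 10.1 says the case report form holds the items the protocol specifies. Whoever builds or completes the form has two conflicting instructions.

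Two things are at stake. First, cases caused by laxatives have nothing to do with the probiotic. If they arise equally in both arms, they pull the difference towards zero. Second, stools are recorded daily but these drugs are scheduled only at visits. Nothing in the protocol ensures that an episode can be set against the drug change before it, so a smaller-than-expected effect would be harder to interpret. Anti-diarrhoeals act differently: they can shorten a recorded episode and so affect the duration endpoint.

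**Working it through.** **1. Which loose stools does each definition count?**

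| Situation | Section 6.1 and synopsis | Sections 5.5.5 to 5.5.7 |
|---|---|---|
| Habitual loose stools on a stable laxative | counted | not counted (not above normal) |
| Two loose stools within 24 hours after a new or increased laxative | counted | counted (above normal) |

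The exclusion in section 5.1.2 of patients with diarrhoea in the 7 days before intervention also removes some patients of the first kind. It does not touch the second.

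**2. The plan's own sample size.** Inputs from section 7.2: 56.3% and 38.4%, alpha 0.05, power 90%. I assume a two-sided test, which the protocol does not state. I take 56.3% as the comparator rate, as the plan does, although section 7.2 describes that group as proton pump inhibitor users. With p̄ = (0.563 + 0.384)/2 = 0.4735,

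n = [1.960·√(2·0.4735·0.5265) + 1.282·√(0.563·0.437 + 0.384·0.616)]² / 0.179² = (1.384 + 0.890)² / 0.0320 ≈ 161.4, so 162 per group.

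Then 162/0.90 = 180 per arm. Both stated figures reproduce, and power at 162 per arm is 90.1%.

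**3. Attenuation if laxative cases come on top of the planning rates.** Let m be the share of patients without true AAD who meet the definition through a laxative, equal in both arms. The documents give no value for m; 5% to 20% is an assumed range. Then p′ = p + m(1 − p) in each arm, so the difference is (1 − m) × 17.9 points. Power = Φ{[d√n − 1.960·√(2p̄′(1 − p̄′))] / √(p₁′(1 − p₁′) + p₂′(1 − p₂′))}, with d = p₁′ − p₂′, p̄′ the mean of the two rates, and n = 162.

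| m | Comparator | LcS | Difference (points) | Power |
|---|---|---|---|---|
| 0 | 56.3% | 38.4% | 17.9 | 90.1% |
| 5% | 58.5% | 41.5% | 17.0 | 86.8% |
| 10% | 60.7% | 44.6% | 16.1 | 83.1% |
| 20% | 65.0% | 50.7% | 14.3 | 74.4% |

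**4. If the pilot rates already contain such cases.** Then 56.3% and 38.4% are what the trial would observe, and planned power stays at 90%. The true rates follow from p = (p′ − m)/(1 − m). At m = 10% they are 51.4% and 31.6%, a difference of 19.9 points. At m = 20% they are 45.4% and 23.0%, or 22.4 points. The trial would then understate the effect on true AAD but lose no power against plan.

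The protocol does not say which case applies. Section 7.2 says only that the rates come from single-site pilot data.

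**The case against.** The case on the other side is substantial.

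- **Laxative data are missing.** A reader might infer this from Appendix 2. The documents do not support it. Section 5.5.2 records laxatives at opening, sections 5.5.5 to 5.5.7 review them at three time points, and Appendix 2 calls itself a summary and has a general medication row at opening. This is an inconsistency to correct, not an absence of data.
- **Episodes cannot be matched to drugs.** This also goes too far. What is reviewed is the inpatient medication chart, which may show earlier use. The protocol does not say that dates are extracted, so matching is not assured; it is not ruled out either.
- **Every laxative-related loose stool counts as AAD.** The procedures require stools above the patient's normal, and recent diarrhoea is excluded. What is left is the new or increased laxative, plus the conflict between section 6.1 and the procedures.
- **Power is lost.** That holds only under an assumed m and only if the pilot rates exclude such cases.
- **Duration is invalid.** Under blinded randomisation and intention to treat, duration under usual care is a legitimate outcome, and anti-diarrhoeal use does not undermine the comparison.
- **Covariates and sensitivity analyses belong in the SAP.** This is fair, and the SAP was not at hand. But no SAP can use dates that were never extracted, and the conflicting definitions and schedule lie in the protocol.

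Randomisation and blinding protect against favouring one arm. They do not prevent dilution by cases that arise equally in both.

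**Conclusion.** The point holds as two inconsistencies with a plausible but unmeasured consequence. Section 6.1 and the synopsis omit a condition that the procedures state three times. Appendix 2 omits laxatives, which the body text requires, and puts anti-diarrhoeals on a coarser schedule than the stools they affect. Even the fuller definition lets through loose stools that follow a new or increased laxative, and the scheduled data do not ensure that these can be recognised.

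The size cannot be derived from the documents. The fall to 17.0, 16.1 or 14.3 points, with power of about 87%, 83% or 74%, rests on three assumptions: m of 5%, 10% or 20%; m equal in both arms, which blinding makes reasonable; and pilot rates free of such events. Without the last, planned power is unaffected. This is a worthwhile, cheap improvement. It does not show that the primary comparison is invalid.

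**What to change.** 1. Reconcile section 6.1 and the synopsis with the episode definition in sections 5.5.5 to 5.5.7, so that one definition of a case applies throughout.
2. Add a laxative row to Appendix 2 to match the body text.
3. Record start, stop and dose-change dates for laxatives and anti-diarrhoeals from the medication charts already under review. This concerns recording only; prescribing stays with the clinicians.
4. Keep the primary analysis on all episodes by intention to treat. Include baseline laxative use in the logistic model of section 7.4.
5. Add one supportive sensitivity analysis, with episodes classified blind to arm, that does not count episodes starting after a new or increased laxative. State its limit: laxative use is post-randomisation and could itself respond to treatment if the study drink affects constipation.
6. Report anti-diarrhoeal use by arm next to duration, as description and not as a correction.

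The cost is some extra data entry and one sensitivity analysis that conditions on a post-randomisation event, so it can support the primary result but not replace it.
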